## Abstract

**Introduction:**

Patient falls in hospitals lead to patient harm, staff distress and economic burden on health systems. There are few strategies with robust evidence demonstrating benefit for the prevention of falls, especially in acute hospital settings. Education and multicomponent fall prevention approaches are promising. Rigorous systematic measurement of implementation has been lacking in most hospital fall prevention trials. This paper describes the protocol for a trial that will evaluate the impact of supported implementation of tailored multicomponent fall prevention interventions on patient falls in hospital.

**Methods and analysis:**

A stepped-wedge hybrid type I effectiveness implementation cluster randomised trial will be conducted. Twelve inpatient wards across four metropolitan hospitals will be enrolled in the trial, clustered into groups of four and randomised to commence the intervention at one of three time periods. Patients and ward staff will be recruited to complete pre-implementation surveys, which, combined with analysis of routinely collected local falls data and staff brainstorming, will inform tailored multicomponent fall prevention interventions for each ward. Wards will receive quality improvement training, clinical facilitation and staff education for at least 4 months to support implementation of their fall prevention interventions. The primary outcome—rate of falls—will be measured using routinely collected hospital falls data from the incident management system and medical records. Pre-implementation and post-implementation patient and staff surveys, qualitative interviews and bedside audits will measure secondary effectiveness and implementation outcomes. Healthcare utilisation from hospital data will inform the cost-effectiveness analysis.

**Ethics and dissemination:**

The Sydney Local Health District Human Research Ethics Committee (RPAH Zone) approved this trial (protocol number X24-0087 and 2024/ETH00583). The trial is registered with the Australian and New Zealand Clinical Trials Registry (ACTRN12624000896572). Data collection commenced in October 2024, due for completion in May 2026. Results will be published in reputable international journals and presented at relevant conferences.

**Trial registration number:**

Australian and New Zealand Clinical Trials Registry (ACTRN12624000896572).

STRENGTHS AND LIMITATIONS OF THIS STUDYThis is a large multicentre stepped-wedge cluster randomised trial including a mix of acute and subacute clinical specialities across 12 wards in four hospitals.The evaluation of effectiveness, implementation and economic outcomes will provide much-needed robust evidence on the effect of tailored fall prevention interventions and implementation strategies; important evidence considering the global ageing population.Falls and fall injury outcomes will be measured via staff-reported data. There is the possibility of increased reporting of falls on wards once they cross over from control periods into intervention periods due to heightened awareness of falls.There are multiple, complex factors influencing hospital falls, and it is not possible to address all of these in this trial (eg, the impact of external contextual factors).

## Introduction

 Falls in hospitals remain a common and costly problem for health systems, health staff and patients and their families.^1 2^ They can lead to significant physical injuries and death, especially in older people.^3 4^ Even without injuries, hospital falls can reduce confidence, activity levels and independence, increase length of stay and alter discharge destinations.^5^ No single approach or intervention has proved a solution for this complex problem across broad acute and subacute hospital patient populations.^6^,^8^ This is reflective of the diversity and complexity of patients and contexts in which falls occur.

The recent World Falls Guidelines highlight the need for hospital fall prevention strategies that are tailored to specific environments and personalised for individual patients.^4^ Tailored multicomponent fall prevention interventions, especially those involving patient education, show a promising impact on hospital falls.^9 10^ However, individualised patient education is time-consuming and unlikely to be cost-effective on acute wards with rapid through-put and a lower total proportion of people who fall in hospital.^11^ Large trials of patient education interventions have also had inconsistent results in patients with cognitive impairment.^9 12 13^ Among hospital inpatients aged 65 and over, 29%–38% are estimated to have cognitive impairment.^14^ One study across a large Australian metropolitan hospital found 43% of inpatients over 65 demonstrated cognitive impairment.^15^ The prevalence of inpatients with cognitive impairment is likely to grow with the growing proportion of hospital admissions by older people.^16^

The implementation of tailored multicomponent fall prevention interventions into routine practice can be challenging and variable.^17 18^ Targeted implementation strategies that are rigorously designed and address barriers to implementation are required to support this process.^2 19 20^ The research team’s prior work explored barriers and facilitators to delivery of multicomponent hospital fall prevention interventions in four local hospital wards, similar in context to the wards planned for this trial.^18 21^ The barriers and facilitators were mapped to the COM-B model of behaviour change to identify suitable implementation strategies targeting ward level capabilities, opportunities and motivation.^22^ The strategies were then tested in a feasibility study in those wards and further refined based on the results. Subsequent mapping (included in online supplemental material 1) identified four core implementation strategies that, when tailored in collaboration with local ward staff to their local context, may support effectiveness of the tailored multicomponent fall interventions in this trial. These include quality improvement training; clinical facilitation; ongoing training and education and building a coalition. These implementation strategies are intended to build workforce capacity for developing and sustaining change.^23^

Economic evaluations are crucial to informing the cost-effectiveness, or value for money, of hospital fall prevention interventions and implementation strategies, thus providing critical evidence for decision-making in policy and practice, especially at scale.^24^ Guidelines for economic evaluation of fall prevention strategies have been available since 2011.^25^ Despite this, few trials of interventions to reduce falls in hospital settings incorporate economic evaluations.^7^

This paper describes the protocol for a stepped-wedge trial that will evaluate whether supported implementation (quality improvement training, clinical facilitation, ongoing training and education and building a coalition) of tailored ward-based fall prevention interventions reduces patient falls in hospitals. The trial will also evaluate the impact of supported implementation of tailored ward-based multi-component fall prevention interventions on a range of secondary effectiveness outcomes, and implementation outcomes and determinants. The cost-effectiveness of the programme from a hospital perspective will also be evaluated.

## Methods

### Study design, randomisation, setting and participants

This study is a stepped wedge pragmatic hybrid type I effectiveness-implementation cluster randomised trial.^26 27^ It has a nested economic evaluation. The trial design involves the random and sequential crossover of clusters of hospital wards from control to intervention units until all units are exposed to the intervention. This study design was chosen as it involves recruitment and intervention implementation at a ward level which, in a context of an intervention that has ward-level impacts, can lead to less bias in the results.^26^ The pragmatic design allows enrolment of diverse patient and staff populations and embeds the research within everyday clinical workflows, enhancing the external validity, generalisability and scalability of the findings.^28 29^ The design also allows for the implementation support to be delivered at staggered times, making delivery more feasible.^30^ This protocol follows the standard protocol items: recommendations for interventional trials statement (online supplemental material 2).^31^ The trial is registered with the Australian and New Zealand Clinical Trials Registry - trial registration number ACTRN12624000896572.^32^

**Figure 1 F1:**
[figure not shown]
Stepped-wedge trial design.

**Figure 2 F2:**
[figure not shown]
Study flowchart. EOI, Expression of Interest.

Staff from nursing, medical, physiotherapy, occupational therapy, dietetics, speech pathology, social work, pharmacy, podiatry, orthotics, diversional therapy, administration and environmental services disciplines working on the participating wards, and inpatients and their family members on the participating wards, will be invited to complete pre-implementation and post-implementation surveys. Given the high turnover of inpatients and staff in many wards and to keep survey responses anonymous, participants in the pre-implementation and post-implementation surveys do not need to be the same. Staff, inpatients and their families will also be invited to participate in post-implementation interviews.

Inclusion and exclusion criteria for the various aspects of the study are provided in table 1.

**Table 1 T1:** Inclusion and exclusion criteria for components of the study

Participants	Inclusion criteria	Exclusion criteria
Hospital wards	Inpatient hospital wards at participating hospitals. Support for nursing and other involved discipline executives to participate in the programme.	Emergency departments. Intensive care units. Paediatric and neonatal wards. Wards currently participating in another research trial with patient falls as a listed outcome. Outpatient settings.
Staff pre-implementation survey participants	Employed by participating hospitals. Work in nursing, medical, physiotherapy, occupational therapy, dietetics, speech pathology, social work, pharmacy, podiatry, orthotics, diversional therapy, administrative or environmental services teams on a ward enrolled to participate in the intervention.	Nil.
Staff post-implementation survey and interview participants	Employed by participating hospitals. Work in nursing, medical, physiotherapy, occupational therapy, dietetics, speech pathology, social work, pharmacy, podiatry, orthotics, diversional therapy, administrative or environmental services teams on a ward that participated in the intervention.	Has worked on the participating ward for <1 week.
Patient and family member/carer pre-implementation and post-implementation survey participants	Admitted inpatient or family member/carer of admitted inpatient on a participating ward at a participating hospital. Deemed cognitively and medically well enough to participate in a survey as per Nurse Unit Manager of the ward’s clinical judgement. Aged 18 years of age and over.	Inpatient on a ward not participating in intervention. Deemed not cognitively and/or medically well enough to participate in a survey as per the Nurse Unit Manager of the ward’s clinical judgement.
Patient and patient family member/carer interview participants	Admitted inpatient or family member/carer of admitted inpatient on a participating ward at a participating hospital. Deemed cognitively and medically well enough to participate in an interview as per Nurse Unit Manager of the ward’s clinical judgement. Aged 18 years of age and over.	Inpatients or visitors on wards not participating in intervention. Deemed not cognitively and/or medically well enough to participate in an interview as per the Nurse Unit Manager of the ward’s clinical judgement. Has been on ward for <24 hours.

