### Implementation outcomes and determinants

Implementation outcomes and determinants will be collected for the tailored fall prevention interventions as well as the implementation strategies. These are outlined in table 3 below, which also summarises the evaluation methods. Methods include quantitative surveys and qualitative interviews with key stakeholders to guide lasting implementation and scale-up,^46 48 49^ as well as address questions about barriers to and facilitators of the approach. Observations on wards, file audits and analysis of study records will also be used. Study records include field notes from study staff documenting timing, attendance and notable moods, dynamics and reflections of meetings and education sessions with participating wards. These measures have been informed by McKay’s implementation framework.^49^

**Table 3 T3:** Overview of implementation measures

	Implementation of tailored ward-based fall prevention interventions	Measurement tool	Delivery of multi-faceted implementation strategy	Measurement tool
Implementation outcomes				
Adoption	Proportion and representativeness of participating ward staff that deliver tailored fall prevention intervention.	Ward-specific audits. Staff surveys.	Proportion and representativeness of the sites that use implementation strategies.	Study records. Staff surveys.
Reach	Proportion of patients provided with fall prevention interventions.	Ward-specific audits. Staff surveys. Patient surveys and interviews.	Proportion of eligible wards who submitted EOIs.	Study records.
Dose	Extent of delivery of selected intervention components.	Ward-specific audits. Staff surveys and interviews. Patient surveys and interviews.	Hours per clinical team of delivered multi-faceted implementation strategies.	Study records/fieldwork notes.
Fidelity	Extent to which selected fall prevention interventions are implemented.	Staff surveys and interviews.	Proportion of intended training, education and facilitation sessions provided to and attended by participating clinical teams.	Study records.
Sustainability	Intended ongoing delivery of fall prevention interventions after the 4-month clinical facilitation period.	Staff surveys and interviews.	Participation in peer support sessions after clinical facilitation period has ceased. Intended use of quality improvement skills in future work.	Study records. Staff surveys.
Implementation determinants				

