#### Survey analysis

All returned surveys that have at least one response will be included for analysis. Descriptive statistics (means, SD, change, counts and percentages) will be used to analyse survey data.

Quantitative implementation analysis of survey data will involve numerical description of quantitative implementation measures, presented as percentages or means and exploration with relative risks. Changes from pre-delivery to post-delivery of implementation strategies in self-reported staff and patient/family surveys will be evaluated using paired-sample t-tests. Univariate correlations will explore changes in these measures.

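### Staff with under one week on the ward may answer the pre-implementation survey but not the post-implementation one, so the tested staff change can carry a (probably small) composition difference

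*Protocol article*

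**What the plan says.** All references are to the protocol article.

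- **Staff, before.** The Table 1 row for the pre-implementation survey ends "environmental services teams on a ward enrolled to participate in the intervention. Nil"; the last word is the entry in the exclusion column. The recruitment section for staff surveys describes flyers with a link and a QR code, and no limit on time worked on the ward.
- **Staff, after.** The Table 1 row for the post-implementation survey and interviews excludes anyone who "Has worked on the participating ward for <1 week".
- **Who answers.** The section on study design and participants says that "participants in the pre-implementation and post-implementation surveys do not need to be the same", citing turnover and anonymity.
- **Analysis.** Under Survey analysis, "Changes from pre-delivery to post-delivery of implementation strategies in self-reported staff and patient/family surveys will be evaluated", by paired-sample t-tests.
- **Patients and families.** One Table 1 row covers the pre and post surveys. Its exclusions begin "Inpatient on a ward not participating in intervention. Deemed not cognitively and/or medically well enough to participate in a survey" and contain no minimum stay. The interview row adds "Has been on ward for <24 hours".

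**The concern.** A before-and-after comparison is readable as change only if the same kind of person could be sampled at both points. Here staff in their first week can enter the before wave and cannot enter the after wave. If they answer differently from established colleagues, part of the measured change reflects who was allowed to answer.

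True pairing would remove the problem, because the same people would stand on both sides. Anonymous surveys whose respondents need not coincide do not provide that. Whether a paired test suits such data is a separate question, not taken up here.

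At stake are the staff items asked in both waves. These may include staff professional fulfilment, listed among the secondary effectiveness outcomes, and clinician self-efficacy in Table 3. The primary outcome comes from incident reports and coded records and is not involved.

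**Working it through.** **1. The plan's own survey figure.** The Sample size section gives an SD of 0.8, a target change of 0.5 points and 80% power, but no survey sample size, so the power cannot be reproduced. For scale only, assuming a two-sided 5% level for the surveys:
- Paired, if 0.8 is the SD of the change: n = (0.8 × (1.96 + 0.84) / 0.5)², which rounds up to 21 pairs (23 with the t distribution).
- Independent waves: n = 2 × (0.8 × (1.96 + 0.84) / 0.5)², which rounds up to 41 per wave (42 with the t distribution).

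**2. Size of the composition shift.** Let f be the share of pre-wave respondents with under one week on the ward, and d the amount by which they score below established staff. The pre-wave mean is then the established-staff mean minus f × d. The post wave contains established staff only, so the apparent change is shifted by f × d: upward if new staff score lower, downward if they score higher.

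The document gives neither f nor d. Assumed ranges are f from 1% to 10% and d from 0.25 to 1.0 point. The shift in points, with its percentage of the 0.5-point target in brackets, is:

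| f | d = 0.25 | d = 0.5 | d = 0.8 | d = 1.0 |
|---|---|---|---|---|
| 1% | 0.003 (0.5%) | 0.005 (1.0%) | 0.008 (1.6%) | 0.010 (2.0%) |
| 2% | 0.005 (1.0%) | 0.010 (2.0%) | 0.016 (3.2%) | 0.020 (4.0%) |
| 5% | 0.013 (2.5%) | 0.025 (5.0%) | 0.040 (8.0%) | 0.050 (10.0%) |
| 10% | 0.025 (5.0%) | 0.050 (10.0%) | 0.080 (16.0%) | 0.100 (20.0%) |

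**3. How plausible the top of the range is.**
- In a steady state, a 5% to 10% share in the first week implies 52 × 0.05 = 2.6 to 52 × 0.10 = 5.2 complete staff turnovers a year.
- An assumed turnover of 50% a year gives 0.5 / 52, about 1%. Rotating or pool staff could raise this.
- A gap of 1.0 point is 1.0 / 0.8 = 1.25 SD.

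The lower rows of f are therefore the likelier ones.

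**4. Against sampling error.** With 41 independent respondents per wave, the standard error of the difference is 0.8 × √(2/41) = 0.177. The largest shift in the table is 0.10 / 0.177 = 0.57 of a standard error; the 0.04 case is 0.04 / 0.177 = 0.23. Larger surveys would shrink the standard error but not the shift.

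**5. The same check for patients.** The survey criteria sit in one row for both waves, so they cannot differ between waves. The 24-hour rule applies to interviews only, and "Staff, inpatients and their families will also be invited to participate in post-implementation interviews": interviews have no pre-implementation wave. No before-and-after mismatch arises.

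**The case against.** **The rule has a reason.** A newcomer cannot rate an intervention not yet met, so excluding first-week staff afterwards is sensible. The pre-survey also feeds each ward's needs analysis, where every member of staff is relevant. Both points stand. They justify collecting the waves under different rules, but not comparing them without a common restriction.

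**The effect is small and its sign unknown.** This also stands. Nothing in the document shows that new staff score lower, so a reader should not infer that the mismatch favours the programme. Nor are new or casual staff barred from the post wave as a class; one week on the ward is enough.

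**The questionnaires are in a supplement that is not shown.** A time-on-ward question may already be there. If so, only the analysis needs changing.

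**A stronger reading about patients.** A reader might infer that surveying patients in their first 24 hours biases patient-reported reach downward, and that the interview exclusion should be copied to the surveys. The document does not support this. Table 3 defines reach as "Proportion of patients provided with fall prevention interventions", with no minimum stay. A short-stay patient who was given nothing is therefore correctly counted as not reached. Excluding such patients would change the quantity measured and could overstate reach where stays are shortest.

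Nor can the share of first-day patients be derived from the Sample size section. Dividing 3 × 14 400 = 43 200 bed days by 5808 patients gives 7.4 days. But 43 200 is 12 wards × 30 beds × 120 days, a single period, whereas the 5808 patients are those expected over the whole study. Over the 5 + 19 = 24 months of extraction, taken as 730 days, 12 × 30 × 730 / 5808 gives about 45 days. Neither is a usable length of stay.

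**Conclusion.** The point holds for the staff surveys only. Table 1 applies different eligibility to the two sides of a comparison that the Survey analysis section plans to test, and anonymous respondents who need not be the same people cannot be matched to undo it.

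The resulting shift is probably small: about 0.003 to 0.10 Likert points, or 0.5% to 20% of the 0.5-point target. That range rests wholly on assumed shares (1% to 10%) and score gaps (0.25 to 1.0 point), and its direction is not known. This is a minor but avoidable flaw in secondary staff measures. It does not touch the falls rate and gives no ground for changing the patient survey criteria.

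**What to change.** - Keep all pre-implementation staff responses for the ward needs analysis.
- For the pre-to-post staff comparison, apply the same exclusion (under one week on the ward) to both waves, and say so in the analysis plan.
- Include one time-on-ward item in the staff survey, if it is not already there.
- Data collection began in October 2024, so some pre-surveys may have been collected without such an item. For those, state the mismatch as a limitation.

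The cost is one survey item at most, one sentence in the analysis plan and slightly fewer pre-wave respondents in the comparison. The patient and family rows of Table 1 need no change on this account.

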### Participant recruitment

#### Recruitment of participating wards

Twelve eligible inpatient hospital wards will be recruited to participate in the PROTECT Fall prevention programme and trial via an invitation to voluntarily submit an expression of interest (EOI). The EOI invitation and a participant information statement (PIS) will be circulated via e-mail by a district Fall Prevention and Management Coordinator to the Nurse Unit Managers and Clinical Nurse Educators of the wards of participating facilities. Wards have 2 weeks to decide if they wish to submit an EOI to participate. Ward teams will be provided with the opportunity to ask questions about the study by contacting the research team and by invitations to attend online drop-in information sessions.

If a ward wishes to participate in the study, they will be asked to return a completed EOI form to the study team. The returned EOIs will be screened to ensure they meet inclusion and exclusion criteria. If more than 12 EOIs are received, a selection of wards that optimise diversity of case mix and facility location will be selected. Wards that submit an EOI with a multidisciplinary team will be prioritised. The Nurse Unit Manager of eligible wards will be invited to provide informed consent for their ward to participate in the trial.

We have received a waiver of consent to collect patient outcome data (via routinely collected hospital data) for inpatients admitted to the participating wards during the data collection period.

